## Abstract

**Background:**

Do fibromyalgia patients have a preferred resistance training volume?

**Purpose:**

This protocol will support a trial evaluating the preference for volume in three different resistance training protocols for women with fibromyalgia.

**Methods:**

Protocol for a randomized crossover clinical trial. Women aged 18–65 years with a diagnosis of fibromyalgia will be included. Patients who have undergone resistance training in the last 6 months, who have another associated rheumatic disease, who have travel or scheduling commitments that will require them to be absent for the next 4 (four) weeks from the start of the study, who have upper and/or lower extremity musculoskeletal injuries, or who have cardiac problems that prevent maximal and submaximal exercise will not be included. The primary outcome will be preference. Secondary outcomes will be expectation, pain intensity, affect, and perceived effort, training volume, and cadence. For the primary outcome, the number of choices of the 3 types of training will be recorded as a percentage. For the analysis of the primary outcome, we will summarize the patient's preference in a contingency table, compare the proportions using the chi‐squared test, and finally verify the effect size of the observed differences. For the secondary outcomes, statistical analyses will be performed by a blind statistician. The independent variables of group and time will be considered for each dependent variable.

**Results:**

This will be the first study to examine the preference of women with fibromyalgia for different volumes of resistance training.

**Discussion:**

We will show whether exercise volume preference is related to subjective perception of exertion and pain intensity in women with fibromyalgia.

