### Statistical Methods

2.18

For the primary outcome (preference), the number of choices of the 3 types of training will be recorded as a percentage. For the analysis of the primary outcome, we will summarize the patient's preference in a contingency table, compare the proportions using the chi‐squared test, and finally verify the effect size of the observed differences. For the secondary outcomes, statistical analyses will be performed by a blind statistician using commercial software. The independent variables of group and time (T0, T1, T2, T3, T4) will be considered for each dependent variable: pain intensity, subjective effort, affect and satisfaction. The Kolmogorov–Smirnov test was used to verify the distribution of the data and the Levene test was used to analyze the homogeneity of variance.

A mixed design analysis of variance will be conducted for the primary and secondary outcomes with a normal distribution, with time as the within‐subject factor and group as the between‐subject factor. If the data are not normally distributed, the Friedman test is used. Time × group interactions and between‐ and within‐group differences were analyzed for all variables. Finally, the Bonferroni test is used in post hoc analyses to determine whether there are differences between‐groups at different intervention times. A 5% significance level and 95% confidence interval will be used for all statistical analyses.

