## Implications of Physiotherapy Practice

5

This protocol will support the first trial examining the preference of women with fibromyalgia for different volumes of resistance training.We will check whether exercise volume preference is related to subjective perception of exertion in women with fibromyalgia.We will check whether exercise volume preference is *related* to pain intensity in women with fibromyalgia.

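### The article promises to relate volume preference to perceived exertion and pain, but no analysis it names links a patient's choice to her own scores

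*Protocol article*

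**What the plan says.** The promise appears in two places. The abstract's Discussion consists of one sentence: "We will show whether exercise volume preference is related to subjective perception of exertion and pain intensity in women with fibromyalgia". Section 5 (Implications of Physiotherapy Practice) says "We will check whether exercise volume preference is related to subjective perception of exertion in women with fibromyalgia" and makes a parallel statement about pain intensity.

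The analyses are in Section 2.18 (Statistical Methods):

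- **Preference:** the stated steps are to "summarize the patient's preference in a contingency table, compare the proportions using the chi‐squared test, and finally verify the effect size of the observed differences".
- **Other outcomes:** "The independent variables of group and time (T0, T1, T2, T3, T4) will be considered for each dependent variable: pain intensity, subjective effort, affect and"; a fourth item, satisfaction, completes the list. The model is a mixed analysis of variance "with time as the within‐subject factor and group as the between‐subject factor". As the alternative, "If the data are not normally distributed, the Friedman test is used". Afterwards "the Bonferroni test is used in post hoc analyses to determine whether there are differences between‐groups at different intervention times".

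The abstract's Methods repeat this split. The note to Table 1 adds only a comparison of session durations between groups. Section 2.17 bases the sample size on the preference proportions alone.

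**The concern.** A relation between preference and exertion or pain is a statement about patients: did a woman tend to choose the session that she herself rated as easier or less painful? To answer it, choice and scores must enter the same analysis. In Section 2.18 they stay apart. Preference has no covariate, and pain and effort have group and time as their only factors.

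An author who follows the listed analyses and then writes up the promised relation has vote shares by protocol and mean scores by protocol, which is three points. Section 2.6 makes number of sets the only training variable that differs between protocols, so a difference in mean effort comes together with a difference in sets. If mean effort rises with sets and votes fall with sets, the totals will look like a link between effort and preference even if no patient chose on effort; session length, for instance, would give the same pattern. The alternative is a patient-level analysis picked after the data are seen.

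**Working it through.** **1. The plan's own figure.** Inputs from Section 2.17: w = 0.8, α = 0.05, 25 degrees of freedom, and 0.80, which is printed as β but works as power. The non-centrality at N = 36 is 36 × 0.8² = 23.04 and the critical value is 37.65, both as printed. Power is 0.804 at N = 36 and 0.789 at N = 35, so 36 is reproduced on these inputs. The calculation concerns preference proportions only and says nothing about an association with effort or pain.

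**2. Promise against analyses.**

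| Analysis named | Outcome | Factors | Links choice to own scores? |
|---|---|---|---|
| Chi-squared with effect size | Preference counts | None | No |
| Mixed ANOVA, or Friedman | Pain, effort, affect, satisfaction | Group, time | No |
| Bonferroni post hoc | Same | Groups at each time | No |
| Durations (Table 1 note) | Session duration | Group | No |

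Section 2.18 also says that the mixed ANOVA covers the primary outcome. That does not change the last column: preference is one categorical answer given once, at the end, and group and time would still be the only factors.

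**3. Are the data there?** Yes. Table 2 has pain before, after and 24 h after each session, affect at the same points, and effort after each session. Section 2.10 asks about expectation separately for 1, 2 and 3 sets. Each patient therefore supplies one choice among three options with scores for each, giving 36 choice sets and 36 × 3 = 108 option records.

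**4. What 36 choices can show.** The documents give no within-patient spread. I assume a standard deviation (SD) between a patient's three options of 1.0 to 1.5 points, with the usual n − 1 divisor. In a conditional logit with one option-specific predictor, at no association and equal choice shares:

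- Information per choice set is the variance with divisor 3, which is (2/3) × SD².
- Total information = 36 × (2/3) × SD² = 24 × SD².
- SE = 1/√(24 × SD²) = 0.204/SD.
- Odds ratio per point detectable with 80% power at two-sided 5% ≈ exp(2.8 × SE).

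| Assumed SD | SE | Detectable odds ratio |
|---|---|---|
| 1.0 | 0.204 | 1.77 |
| 1.2 | 0.170 | 1.61 |
| 1.5 | 0.136 | 1.46 |

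**5. Unequal choices.** The plan sizes for w = 0.8. A split of 71%, 14.5% and 14.5% has that size: √{3 × [(0.710 − 0.333)² + 2 × (0.145 − 0.333)²]} ≈ 0.80. With set effects held fixed at that split, the factor 2/3 becomes 1 − (0.71² + 2 × 0.145²) = 0.454. The SE is then 1/√(36 × 0.454 × SD²), which is 0.247 at SD 1.0 and 0.165 at SD 1.5, with detectable odds ratios of about 2.0 and 1.6. Estimating the set effects while effort is correlated with sets would raise these further.

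**The case against.** The strongest reply is that this is an omission in a condensed article. The purpose, and the hypothesis at the end of the Introduction, concern preference alone; the outcomes and sample size mention no association; and the model for an exploratory association is the kind of detail that a separate analysis plan may hold. The first part stands: this is a secondary promise, and a reader who takes it for the trial's main aim goes too far. The second part stands only partly. The article is not silent on method. It names the factors for pain and effort, and those factors cannot produce the promised relation.

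A second reply is that group might mean the group of patients preferring a given option. That would fit a between-subject factor, since every patient performs all three protocols, and the ANOVA would then address the promise. But Section 2.18 does not define the term, and the note to Table 1 uses groups for the training protocols. Nothing in the document supports the other reading.

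Two stronger readings should be set aside. A reader might infer that the trial cannot answer the question; Table 2 shows that the data will exist, so the gap lies in the named analyses only. A reader might also infer that every listed analysis compares protocols and nothing else; time and its interaction with group are tested too, although these terms do not involve preference either.

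Finally, the conditional logit is one choice among several. Comparing each patient's score for her chosen option with her mean for the other two would also serve.

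**Conclusion.** The mismatch holds. Two sections commit the trial to reporting whether preference is related to exertion and pain, and no named analysis relates a patient's choice to her own ratings. What remains is an aggregate comparison over three protocols, with effort and number of sets confounded. This does not threaten the primary analysis of preference counts. It deserves correction because a sentence in the abstract would otherwise rest on an uninformative comparison or on a method chosen afterwards.

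The defect itself is not numerical. The figures describe only what a repair could deliver: a detectable odds ratio of roughly 1.8 to 1.5 per point. They rest on the assumed SD, equal choice shares, a single predictor, all 36 patients giving a choice, and information evaluated at no association. Unequal shares or adjustment for sets would push them higher. Only fairly strong associations would be detected, so a null result would not show that preference is unrelated to effort or pain.

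**What to change.** Add one paragraph to Section 2.18 that pre-specifies an exploratory patient-level analysis. An example is a conditional logit with the patient as stratum, the option chosen at the final assessment as outcome, and option-specific predictors entered one at a time: effort rating, pain change from before to after the session, and pain change from before to 24 h after. Report odds ratios per point with 95% confidence intervals, labelled exploratory.

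Without adjustment, the estimate still includes whatever number of sets contributes to both effort and choice. A second fit with indicators for number of sets would separate the two as far as the data allow, at a further loss of precision. State which fit supports which conclusion.

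If the authors do not want this analysis, they should withdraw or soften the sentences in the abstract's Discussion and in Section 5.

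Either route needs no new data, visits or patients. Section 2.6 places the conduct of the research after publication of the protocol, so on the document's own account the change can be made before outcome data exist. The cost of the first route is low precision, which the report should state.

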**Trial Registration:**

ClinicalTrials.gov (Identifier: NCT06424743)

## Introduction

1

Fibromyalgia is a painful syndrome of unknown etiology that affects at least 2% of the world's population (Häuser et al. 2015). Although pain is a major symptom, other symptoms such as non‐restorative sleep, fatigue, and mood disturbances are common (Pontes‐Silva, Nunes, et al. 2023). The benefits of resistance training for patients with fibromyalgia have been well established in the literature and include: improvement in pain, function, quality of life, pain points and physical conditioning (Häuser et al. 2015).

Recent evidence underscores the intricacy of fibromyalgia's pathophysiology. This includes dysfunctions in central nervous system pain modulation, neuroinflammation, and altered hypothalamic–pituitary–adrenal axis activity. These factors collectively help to explain the persistence and multisystemic nature of symptoms. These findings underscore the importance of non‐pharmacological approaches that address not only symptoms but also the broader biopsychosocial context of the disease. In this regard, physical exercise, including resistance training, is a key therapeutic strategy due to its potential neurophysiological benefits beyond symptom relief (González‐Álvarez, Riquelme‐Aguado, Rossettini, et al. 2024).

Although resistance training is currently part of the accepted non‐pharmacological treatment for fibromyalgia, we do not have concrete guidelines regarding its prescription in terms of acute training variables such as intensity, order of exercises, speed of execution, type of exercise, and training volume (Macfarlane et al. 2017). Assuming the importance of the acute variables of resistance training, which have already been recognized and studied, it is reasonable to accept that the training volume is equivalent to the dose of a medication, where the variation of this prescribed amount will produce different results in individuals (Schoenfeld et al. 2017).

From an exercise science perspective, training volume—typically defined as the total amount of work performed (sets × repetitions × load)—has been consistently associated with the magnitude of physiological adaptations. This finding reinforces the idea that training volume is a primary determinant of efficacy (Schoenfeld et al. 2017). Another study observed significant benefits with varying volumes of resistance training in clinical populations such as those with fibromyalgia (Forner‐Álvarez et al. 2024).

This suggests that volume modulation can be viewed similarly to medication dosage, where specific amounts yield different therapeutic effects. This analogy supports the idea that prescribing volume, rather than intensity, plays a central role in optimizing the safety and efficacy of resistance training for patients with fibromyalgia (Schoenfeld et al. 2017; Forner‐Álvarez et al. 2024).

Muscle dysfunction, including mitochondrial alterations and reduced oxidative capacity, has been reported in patients with fibromyalgia. This dysfunction contributes to fatigue, pain, and exercise intolerance. These impairments underscore the importance of resistance training as a treatment for these symptoms and as a means of improving muscle health and energy metabolism in these individuals. It is crucial to understand this muscular profile when tailoring resistance training programs to avoid overexertion and enhance adherence (González‐Álvarez, Riquelme‐Aguado, González‐Pérez, et al. 2024).

Given the high dropout rate and the belief among fibromyalgia patients that exercise worsens their symptoms, an incorrect dosage may cause the patient to abandon the exercise program, in addition to creating a negative exercise experience (Vancampfort et al. 2024). The current literature still does not provide clear guidance on what exercise volume can be used for fibromyalgia patients. This gap presents a barrier for clinicians prescribing and supervising resistance training for this type of population (Pontes‐Silva, Dibai‐Filho, et al. 2023).

Although the benefits of exercise are evident, there is wide variability in how individuals respond, and many patients still struggle to adhere to an exercise regimen. A recent systematic review revealed that physical and psychological barriers, such as pain during or after exercise, fear of worsening symptoms, and lack of motivation, significantly impact exercise adherence in patients with fibromyalgia. This underscores the importance of considering not only physiological outcomes but also patient experience and engagement with the training process (Viceconti et al. 2022).

In addition, some studies that have demonstrated the efficacy of resistance training have found that even when we find an effective dose for treating fibromyalgia patients, this appropriate dose does not guarantee that the patient will adhere to regular resistance training (Rausch Osthoff et al. 2018). In general, the dose of resistance training meets only two implications: the positive result of this prescribed dose (the result, i.e., whether this dose improves the symptom, in the case of fibromyalgia) and the safety (absence of injury or a very low percentage) of this dose (Ekkekakis et al. 2011).

In contrast, when exercise prescription is effective and safe, the results themselves do not guarantee reproducibility for other contexts and populations, depending exclusively on the patient's will (i.e., the specificity of each individual). Among the many individual specificities, we highlight patient preference, which has been recommended for over 2 decades, as it is one of the pillars of evidence‐based practice (Garber et al. 2011). In addition, patient preference is a specific recommendation for fibromyalgia (Macfarlane et al. 2017; Rausch Osthoff et al. 2018).

Patient‐centered approaches, particularly those that consider individual preferences, have become increasingly important in fibromyalgia management. Recently, experts have recommended personalized exercise interventions based on patient goals, symptoms, and preferences to optimize long‐term adherence and clinical outcomes. These recommendations align with evidence‐based practices and justify exploring how specific variables, such as training volume, align with patient preferences (Viceconti et al. 2021).

The literature has already demonstrated positive results in relation to the most varied training volumes in patients with fibromyalgia, and how to plan an intervention program; however, there are no studies with more specific investigations in relation to the volume of resistance training and the preference of patients with fibromyalgia (Pontes‐Silva, Dibai‐Filho, et al. 2023). Thus, under the scientific hypothesis that women with fibromyalgia prefer lower volumes of resistance training, this protocol will support a trial evaluating the preference for volume in three different resistance training protocols for women with fibromyalgia.

## Methods

2

### Trial Design and Setting and Ethics Aspects

2.1

The protocol for a randomized crossover clinical trial (ClinicalTrials.gov: NCT06424743) was approved by the Research Ethics Committee of the Universidade Federal do Rio Grande do Norte (report number: 6.303.419), Brazil. The SPIRIT 2025 Statement was used (Hróbjartsson et al. 2025). The trial will be reported according to the Consolidated Standards of Reporting Trials and the exercise program according to the Template for Intervention Description and Replication (Schulz et al. 2010; Hoffmann et al. 2014).

### Patient, Public Involvement, and Recruitment

2.2

Patients will be recruited through social media promotion of the research. Initial contact will be made by Researcher A by telephone to schedule the screening. If eligible, patients will be informed of the objectives and procedures of the study and will sign an informed consent form without any influence from the researcher. Sociodemographic and fibromyalgia impact data will be collected. Patients' personal data will be numerically coded and stored in a database to maintain blinding of the study (Figure 1).

**FIGURE 1 pri70101-fig-0001:**
[figure not shown]
Flowchart. T1: Assessment will be performed respecting a 7‐day interval after the baseline assessment. T2 and T3: assessments will follow the same procedure as T1, with a 7‐day interval between each protocol (T1, T2 and T3), so that the patient will perform the other two training protocols. T4: assessment one week after the T3 assessment.

### Eligibility Criteria

2.3

Women aged 18–65 years with a diagnosis of fibromyalgia according to the 2016 American College of Rheumatology criteria will be included (Wolfe et al. 2016). Patients who have undergone resistance training in the last 6 months, who have another associated rheumatic disease, who have travel or scheduling commitments that will require them to be absent for the next 4 (four) weeks from the start of the study, who have upper and/or lower extremity musculoskeletal injuries, or who have cardiac problems that prevent maximal and submaximal exercise will not be included.

### Harms and Research Team

2.4

This randomized crossover clinical trial will involve five researchers who will perform the following functions: (A) screening and blinded assessment of patients; (B) randomization of patients; (C) monitoring of training protocols; (D) tabulation of data collected during assessments; and (E) statistical analysis.

### Randomization, Allocation, Blinding, Patient Timeline, and Data Collection Methods

2.5

Randomization will be performed before each training protocol, taking into account the 3 different types of training protocols. The order in which the patient will perform the training protocol will be determined by a simple draw in an envelope containing 3 papers described as 1 series, 2 series, or 3 series. Therefore, if in the first session the patient draws the paper described as 1 series, in the following week this paper will be removed from the envelope and the same will draw 2 or 3 series, and so on.

In this way, all patients involved in the study will randomly perform the 3 types of protocols proposed in the study, and they will be their own controls. To avoid allocation bias, opaque sealed envelopes will be used, with sequential numbers on the outside of the envelope. This allocation will be made by Researcher B, who will not be involved in any other study procedures. Patients selected in the screening conducted by Researcher A who agree to participate in the research will be randomly assigned.

Regarding blinding, all assessments will be performed by Researcher A, who will not be involved in the interventions and will not participate in the delivery of the training protocol. Each patient will remain identified by numbers and not by name. In order not to compromise the blinding of the study, all patients will undergo the same assessment before and after the training session. Due to the nature of the proposed intervention (physical exercise), the therapist and patients will not be blinded to the intervention. Patients will be instructed not to disclose any information to other patients and/or researchers.

At the end of the T3 training protocol, with a 7‐day interval between these assessments, we will conduct T4, where each patient will be asked which training protocol they prefer. After T4, researcher D will tabulate the data, which will be delivered to researcher E, who will be responsible for the statistical analysis and who will not participate in the previous phases of the research (Figure 2).

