**FIGURE 3 pri70101-fig-0003:**
[figure not shown]
Proposed exercises.

The T1 assessment will be performed respecting a 7‐day interval after the T0 assessment. At this interval, the patient will return and we will perform the first training protocol drawn on that day (T1). In addition, we will collect the following variables: pain intensity and affect before and after training, total training volume, and subjective effort after training.

The T2 and T3 assessments will follow the same procedure as T1, with a 7‐day interval between each protocol (T1, T2 and T3), so that the patient will perform the other two training protocols. The protocol draw will take place on the respective days of each assessment (T2) and (T3). If the envelope of the protocol drawn has already been performed on previous days, the patient will be instructed to perform a new draw.

Finally, at the T4 assessment, one week after the T3 assessment, the patient will be asked by telephone by the same evaluator (T0 baseline) about his preference for the programs performed in the study (with 1, 2 or 3 sets), standardizing the same commands used in person throughout the study. The following is a description of the three types of training programs with different volumes. The only different training variable will be the number of sets in the three training protocols of the study (Table 1).

**TABLE 1 pri70101-tbl-0001:** Training protocol.

Training (protocol)	Exercise	Sets (*n*)	Repetitions (*n*)	Load (1RM)	Rest (minute)
1	1–4	1	10	60%	2
2		2			
3		3			

*Note:* 1RM: One‐repetition maximum test. Each patient will receive the exercise session individually, as each of the three training protocols has different volumes (i.e., 1, 2, or 3 sets), consequently, the durations will vary for each patient; and then the durations will be compared between the groups.

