### Sample Size

2.17

Sample size calculation was performed a priori using G*Power software (version 3.1.9.7) with the Chi‐squared test for comparisons between the proportions of self‐reported preferences observed in the contingency tables. We calculated the sample seeking an effect size of 0.8 in the difference in the primary outcome (preference). That is, *w* = 0.8, α = 0.05, β = 0.80, degrees of freedom = 25, non‐centrality parameter λ = 23.04, and critical Chi‐squared test = 37.65 (Gignac and Szodorai 2016; Pontes‐Silva 2023). Thus, the sample was estimated to be 36 patients.

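### Session order is set by an unrestricted draw, so the six orders will almost surely be unbalanced in 36 patients; a blocked six-order list, with a primary test that respects it, removes avoidable noise but corrects no bias

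*Protocol article*

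**What the plan says.** Section 2.5 of the protocol article states: "Randomization will be performed before each training protocol". The order is "determined by a simple draw in an envelope containing 3 papers described as 1 series, 2 series, or 3 series". After a session, "in the following week this paper will be removed from the envelope and the same will draw 2 or 3 series". The envelopes are described so: "opaque sealed envelopes will be used, with sequential numbers on the outside of the envelope". Researcher B makes the allocation and does nothing else in the study.

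Section 2.6 describes the T2 and T3 draws again: "The protocol draw will take place on the respective days of each assessment". There, if a protocol already performed comes up, "the patient will be instructed to perform a new draw".

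Neither section mentions blocks, a Latin square or a prepared list of orders. Section 2.17 gives the size: "the sample was estimated to be 36 patients".

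Preference is one choice among the three sessions, asked by telephone at T4, a week after T3 (sections 2.6 and 2.9). Section 2.18 compares the preference proportions with a chi-squared test. For the secondary outcomes it names group and time (T0 to T4) as independent variables.

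**The concern.** A three-period crossover usually balances order by design. Here each patient's order is an independent draw. The opaque numbered envelopes conceal the allocation but do not balance it.

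Position could matter for this outcome. Sessions are 7 days apart, so when the question is asked the last session is one week old, the second two weeks and the first three weeks. A tendency to favour the most recent session is plausible. If one volume happens to come last more often than the others, its share of choices moves for a reason unrelated to volume, and the primary test has no term that accounts for it. At stake are some precision and an order explanation that a reader of the results could raise.

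**Working it through.** **Inputs.** N = 36 (section 2.17), three volumes, one order per patient (sections 2.5 and 2.6). The documents give no recency rate, no position effect on pain and no dropout rate; the values used below are assumptions.

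**Stated N.** With w = 0.8, λ = 36 × 0.8² = 23.04. With df = 25 the critical value is 37.65 and power is 0.804 at N = 36 (0.789 at 35). So 36 reproduces. Whether df = 25 suits a three-option question is a separate matter.

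**Probability of each order.** If the used paper is removed, it is 1/3 × 1/2 × 1 = 1/6. If it stays and a repeat is redrawn, each unused protocol at T2 has probability (1/3)/(2/3) = 1/2, which again gives 1/6.

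**Balance under the draw.** Order counts are multinomial (36; six cells of 1/6). Last-position counts are multinomial (36; three cells of 1/3).

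- P(6 patients in every order) = 36!/(6!)⁶ ÷ 6³⁶ = 0.00026.
- P(each volume last 12 times) = 36!/(12!)³ ÷ 3³⁶ = 0.0226, so P(unequal) = 97.7%.
- Gap between the most and least frequent last volume: mean 5.9 (on average about 15 v 9); P(gap ≥ 6) = 0.49; P(gap ≥ 8) = 0.28.
- P(some order has 2 or fewer patients) = 0.27 (simulation).

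**Effect on one realised trial.** Suppose a fraction r simply choose the latest session. A 15 v 9 split then moves the difference between two shares by r × (15 − 9)/36: 3.3 percentage points at r = 0.2 and 5.0 at r = 0.3.

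**Variance of a share, with no volume preference.** Under the draw, the variance of a count is 36 × 1/3 × 2/3 = 8. Under exact balance, 12 patients have a given volume last and choose it with probability h = r + (1 − r)/3; the other 24 choose it with probability l = (1 − r)/3. The variance is 12h(1 − h) + 24l(1 − l).

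| r | Balanced variance | Ratio to 8 | SD of a share, draw v balanced (points) |
|---|---|---|---|
| 0.2 | 7.68 | 0.96 | 7.9 v 7.7 |
| 0.3 | 7.28 | 0.91 | 7.9 v 7.5 |
| 0.5 | 6.00 | 0.75 | 7.9 v 6.8 |

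**Plain three-category chi-squared test (df 2, N = 36, simulated).** With no true preference it rejects in about 6% of trials under the draw at every r. On balanced orders it rejects in about 5.3%, 4.5% and 2.3% at r = 0.2, 0.3 and 0.5. With an assumed true preference of 50/30/20, power (draw v balanced) is about 0.37 v 0.36, 0.30 v 0.28 and 0.18 v 0.12.

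**Secondary outcomes, pain as example.** Assume SD 2, within-patient correlation 0.6 and a 1-point first-session effect. The variance of the 3-set v 1-set contrast under balance is 2 × 2² × (1 − 0.6)/36 = 0.0889, SD 0.298. Unadjusted under the draw, add 36 × (2/3)/36² = 0.0185: SD 0.328. With period fitted, the SD is about 0.30 under either scheme.

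**Dropout.** With 10% or 20% assumed dropout, the mean last-position gap is about 1.7 or 2.3 patients from a blocked list, against 5.6 or 5.2 from the draw.

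**The case against.** The strongest reply is that simple randomisation is valid. That stands. A reader might infer that the imbalance biases the preference result, but which volume comes last is decided by chance, and the chi-squared test holds its 6% rejection rate at every recency rate tried.

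A reader might also infer that no planned analysis deals with position. That is right only for the primary test. Section 2.18 names time for the secondary outcomes, and each of T1, T2 and T3 holds one session, so time at those visits is period. Once it is fitted, the loss in the pain example nearly vanishes. The text does not say that this is the intent, however, and the Friedman fallback has no place for a period term.

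Nor do the two descriptions of the draw yield different allocations: both give 1/6 per order. They are different procedures and should be reconciled, nothing more. First exposure is also a weaker argument than it looks, because at T0 every patient is familiarised with the exercises and performs as many repetitions as she can on each (sections 2.6 and 2.8).

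Finally, blocking alone is not a free gain. With the plain chi-squared test unchanged, balanced orders give no extra power, and they lose power when recency is strong. This stands, and it shapes the fix.

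**Conclusion.** The point holds as an avoidable loss of balance. Imbalance of some size is almost certain, and about even odds favour a last-position gap of 6 or more; these figures need only N = 36 and independent draws. What the imbalance costs depends on a recency rate that the documents do not give: 4%, 9% or 25% of the variance of a preference share at assumed rates of 20%, 30% or 50%, and only if the primary test can use the smaller variance. Little is gained for the secondary outcomes once period is fitted. Balance is exact only if all 36 patients complete. The change is worth making because 36 is exactly six blocks of six and the remedy needs no extra patients, visits or sessions.

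**What to change.** 1. Replace the draw and redraw text in sections 2.5 and 2.6 with one computer-generated list of the six orders (123, 132, 213, 231, 312, 321) in permuted blocks of 6, held only by Researcher B. Each numbered opaque pack contains three sealed visit cards, opened at T1, T2 and T3.
2. Analyse preference with a test that respects the balanced design. One option is a re-randomisation test that redraws the orders within blocks while holding each patient's chosen position fixed; another is a test stratified by last-session protocol. Report the preferred protocol cross-tabulated by its position.
3. In section 2.18, state that time at T1 to T3 is period and is fitted alongside protocol for the secondary outcomes.

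The cost is minutes to prepare the list and a short edit, best made before enrolment. Section 2.6 places the research after publication of the protocol. The small downside is that the end of a block can be guessed if the block size is known, so it should be kept from Researcher A, who screens patients.
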